### Study design

This study will use a tiered approach (working together with anchor partners who liaise with local community organizations) to distribute COVID-19 tests in Merced County and Pitt County. This protocol draws from HIV detection and treatment interventions [13, 17], and combines community engagement strategies developed through the toolkit. Two anchor partners (Merced County United Way and Pitt County Health Department) will each coordinate directly with up to 10 local partners to distribute 20,000 COVID test kits (40,000 total tests for the study) at community-based testing events (location and timing based on community partner guidance) over a 15-month period. All eligible consented participants at testing events will, using the Colectiv app, complete basic data collection including demographics, COVID-19 testing and treatment questions, additional testing satisfaction survey questions, and contact information. Community partners will also complete feedback surveys using the Colectiv app. All participants will receive compensation. Additionally, participants will receive guidance on COVID-19 mitigation, links to health-promoting resources, and accessible and affordable therapeutics if they test positive for COVID-19. We will leverage the You and Me Healthy Direct-to-Participant Registry (YMH registry) to provide resource linkages to trusted health services in local areas as identified by anchor institutions. The YMH registry provides ongoing notification to participants that they are eligible for enrollment in new research studies related to COVID-19, health equity, and reducing health disparities for underserved populations. For individuals without insurance, participants will be connected to local resources including mobile health clinics (typically serving under- and uninsured individuals) and community health centers. Additional local resources, such as pharmacies, fire departments, and churches offering free testing and treatment, will be identified by our anchor partners.

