### Analysis

We will conduct a comprehensive summary of all collected data including basic descriptives on demographics, test results, treatment, and beliefs (regarding vaccination and treatment), and associations between test results and behavioral measures and access to treatment will be explored using mixed modeling techniques to account for within-participant correlations. Analyses will be conducted using SAS 9.4 (SAS Institute, Cary NC).

We will report the total number of tests distributed and summarize participant characteristics using standard summary statistics and graphical techniques. The number of disseminated tests and consented participants by community, anchor partner, local partners, and specific distribution events or locations will be provided. We will also report the proportion (with 95% exact confidence intervals) of positive tests. Data may be stratified by participant and community partner characteristics and by distribution event. In addition, we will report 1) the proportion of participants who are provided with information on next steps for COVID-19 mitigation and information on accessible treatment locations (as determined by the anchor partner in collaboration with local community partners) within 5 days of reporting a positive test result, and 2) self-reported treatment utilization (type, duration). Lastly, we will conduct hypothesis testing and multivariable modeling using appropriate methods (e.g., mixed logistic and Poisson regression) to explore adjusted relationships between community/participant characteristics and outcomes (test positivity, behaviors, and care access). We will report regression coefficients when models meet assumptions and fit.

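### The only correlation the Analysis section names is within-participant, yet it plans tests of community characteristics in a study clustered by event, local partner and two counties

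*Protocol article*

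**What the plan says.** All statements are from the Methods of the protocol article.

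- **Analysis, opening paragraph.** Associations of test results with behavior and treatment access will be explored "using mixed modeling techniques to account for within-participant correlations". No other source of correlation is named in the article.
- **Analysis, end of second paragraph.** A separate sentence promises "hypothesis testing and multivariable modeling using appropriate methods (e.g., mixed logistic and Poisson regression") in order to "explore adjusted relationships between community/participant characteristics and outcomes (test positivity, behaviors, and care access"). It does not list the random effects.
- **Analysis, on partner characteristics.** These appear in one place only: "Data may be stratified by participant and community partner characteristics and by distribution event".
- **Study design.** "Two anchor partners (Merced County United Way and Pitt County Health Department) will each coordinate directly with up to 10 local partners". That makes one anchor per county.
- **Settings, participants and recruitment.** Enrolment takes place at partner-run distribution events, some of which may be chosen because infection risk or the vulnerability of attendees is high.

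**The concern.** The design is a hierarchy: tests within participants, participants within events, events within local partners, partners within two counties. A participant-level random effect deals with repeated records from one person. It leaves two people enrolled at the same event, or through the same partner, as independent observations. Because events may be picked for their risk profile, positivity could well differ between them for reasons no covariate captures. For a covariate that is constant within an event or partner, the information comes from the number of events or partners, not the number of people. A model without those levels therefore claims too much precision.

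The county level raises a different problem. The article uses the word community for the two counties, both where it explains why they were selected (Background) and where it describes remote working (Discussion). On that reading a community characteristic takes two values. Anchor organization, state, ethnic composition, insurance coverage and vulnerability index all change together between Merced and Pitt.

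At stake is whether reported associations with community characteristics, which the study intends to disseminate, can be read as evidence about those characteristics.

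**Working it through.** The article states no ICC, alpha, power or effect size, so there is no design figure to reproduce. Its own counts agree: 2 × 10 = 20 local partners and 2 × 20,000 = 40,000 tests.

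**Inputs from the article:** up to 20 local partners (Abstract, Study design); 684 enrolled to 3 July 2023 (Discussion).

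**Assumed:** ICC from 0.01 to 0.10; two-sided 5% tests; equal cluster sizes; all 20 partners active.

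**Step 1. Cluster size.** m = 684/20 = 34.2 participants per partner.

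**Step 2. Design effect for a covariate constant within partner.** DEFF = 1 + (m − 1) × ICC. For example, at ICC 0.02: 1 + 33.2 × 0.02 = 1.66.

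**Step 3. Actual error of a nominal 5% test that ignores partner.** Error = 2 × [1 − Φ(1.96/√DEFF)]. At ICC 0.02: 1.96/1.29 = 1.52, giving 12.9%.

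| Assumed ICC | DEFF | True SE / naive SE | Actual error |
|---|---|---|---|
| 0.01 | 1.33 | 1.15 | 8.9% |
| 0.02 | 1.66 | 1.29 | 12.9% |
| 0.05 | 2.66 | 1.63 | 22.9% |
| 0.10 | 4.32 | 2.08 | 34.6% |

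**Step 4. Fewer active partners.** With 10 partners, m = 68.4 and the errors become 13.0%, 20.1%, 34.8% and 48.1%.

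**Step 5. Simulation check.** A beta-binomial simulation used 20 partners of 34 participants, an assumed positivity of 10% and 20,000 runs per ICC. The test that ignores partner rejected in 8.7%, 13.0%, 22.5% and 34.9% of runs. A t test with partner as the unit rejected in 4.8%, 5.0%, 4.6% and 4.6%. Using the right level restores the nominal error even with only 20 clusters.

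**Step 6. County level.** There are two county units. An intercept and one county contrast use both, so 2 − 2 = 0 between-county degrees of freedom remain. The contrast itself has an estimate. Splitting it among county or anchor traits is impossible under any choice of random effects.

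**The case against.** The strongest reply is that a reader might infer that the models ignore clustering, so that their standard errors are wrong. The text does not say so. The within-participant wording is attached to the sentence in which "associations between test results and behavioral measures and access to treatment will be explored"; the models for community and participant characteristics come later and are described by open examples. A mixed model may well include partner or event effects, and a condensed article can leave such detail to an analysis plan that is not shown. This stands: the loss of precision in the standard errors is conditional on no such term being fitted.

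Three other stronger readings also fail:

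- **Partner characteristics are tested.** The article names them only for optional stratification. The error rates above show what ignoring partner would do to a covariate at that level; they are not the error of a stated test.
- **County effects cannot be estimated.** A Merced–Pitt contrast can be. Attribution to a particular trait, and generalization beyond the two counties, are what fail.
- **No community characteristic can be studied.** Characteristics measured below county level can be.

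It is also fair to say that 684 is interim enrolment in a 15-month distribution period, that the Discussion reports difficulty onboarding partners in one county, and that outcomes such as positivity rest on fewer people than were enrolled. These push cluster size in both directions, so no single error rate is established. Finally, the analyses are exploratory and no sample size or primary outcome depends on them.

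What the reply does not reach is the county point. It follows from having two counties with one anchor each, which no unseen analysis plan can alter.

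**Conclusion.** The point holds in two parts.

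First, conditionally: the one dependence named is not sufficient for this design, and omitting event and partner terms would understate standard errors for covariates varying at those levels. The understatement is material even at a small ICC, from a factor of 1.15 at 0.01 to 2.08 at 0.10, under the assumptions of 20 equal partners and interim enrolment. The size depends wholly on the ICC, which the article does not give.

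Second, unconditionally: a test of a county or anchor characteristic is a single Merced–Pitt comparison under another name.

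The exploratory status limits the consequences. It does not remove them, since hypothesis tests are explicitly planned. The change is worth making, but nothing in the study's conduct turns on it.

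**What to change.** Revise the Analysis text so that:

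1. the models account for clustering by local partner and distribution event as well as participant, through random intercepts or a cluster-robust variance, in either case with a small-sample correction because there are at most 20 partners;
2. county enters as a fixed effect;
3. differences between counties or anchors are reported descriptively, and no county characteristic is tested;
4. any community covariate is measured below county level, with clustering at that level. Zip code is one candidate: Table 3 shows 38 codes among 575 of 684 participants, so 109 (684 − 575; 16%) would lack it.

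No new data collection is evident for items 1 to 3, because the Analysis section already promises counts by community, anchor, local partner and event. The cost is a change of wording and model code, wider intervals, no tests of county characteristics, and incomplete data if zip code is used.

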### Dissemination strategy

Because the Colectiv platform allows for real-time aggregate review of data, we will provide our participants with frequent aggregate data summaries that highlight study progress. Once our analysis is completed, we will prepare results in lay-friendly formats for dissemination to maximize public health impact. These will be shared through the YMTT and RADx-UP Coordination and Data Collection Center websites and social media channels, and returned directly to participants via the YMTT participant newsletter.

## Discussion

Community-engaged research relies on authentic and robust partnerships [19]. Collaborations across academic and community organizations are critical to promoting equitable access to health care for underserved communities. However, establishing these partnerships requires copious time, ample resources, and consistent investment from all partners to achieve success. Academics and other researchers can offer helpful expertise and skillsets, although they likely would not have established the necessary partnerships with local organizations and key stakeholders for those interventions to be effective. The Community Engagement Toolkit presents a tiered model for supporting timely interventions in underserved communities in response to widespread health events. The toolkit leverages anchor institutions that have trusted relationships already established with local community partners, who in turn are trusted by the communities that they serve. Through this approach, YMTT offers a case study for community-engaged health disparities research that is effective, timely, and consistent with the need for academic partners to support and follow the lead of local community organizations and stakeholders to effect change.

Adopting this tiered model for community-engaged research, the YMTT study has enrolled 684 participants to date (66.3% female; 72.4% White, 4.3% American Indian or Alaska Native, 3.8% Black, 1.3% Asian; 93.3% Hispanic; 75.4% adults; 59.6% English language preference) from March 24, 2023, through July 3, 2023 (see Table 3).

**Table 3 Tab3:** Demographics and other characteristics for YMTT survey participants (*N* = 684)

Characteristic	n (%)
Age, years (*n* = 684)	
≥ 18	516 (75.4)
< 18	168 (24.6)
Gender identity term (*n* = 584)	
Woman	387 (66.3)
Man	194 (33.2)
Other^a^	3 (0.5)
Race^b^ (*n* = 373)	
White	270 (72.4)
Other/multiple	67 (16.9)
American Indian or Alaska Native	16 (4.3)
Black or African American	14 (3.8)
Asian	5 (1.3)
Native Hawaiian or Other Pacific Islander	1 (0.3)
Ethnicity (*n* = 537)	
Hispanic/Latino/Spanish	501 (93.3)
Not Hispanic/Latino/Spanish	36 (6.7)
Language of survey completed^c^	
English	408 (59.6)
Spanish	276 (40.4)
Where they heard about test kit distribution^b^ (*n* = 575)	
A community organization	517 (89.9)
Word of mouth	44 (7.7)
Social media	14 (2.4)
Other	12 (2.1)
Flyer	11 (1.9)
Community bulletin board	10 (1.7)
Total number of zip codes represented (*n* = 575)	38

^a^Includes “gender non-binary/genderqueer/gender nonconforming,” “two-spirit,” and “none of these describe me.”

^b^Participants could indicate all answer choices that applied

^c^Participants could select whether to complete the survey in English or Spanish

Participants on average have rated the experience of acquiring the COVID-19 test kit as 9.2 on a 1–10-point scale, with 10 being the highest satisfaction with the experience. YMTT also has held biweekly anchor and community partner meetings to support implementation, troubleshoot challenges with recruitment and data collection, and share best practices. Routine and open dialogue with the community partners also led to the development of narrated videos for both community partners and participants to support enrollment and use of the Colectiv app, specific newsletter content, anchor partner–led trainings for local partners on study enrollment, and tailoring communications materials to provide simpler and more direct messaging.

The YMTT study has strategized to address several challenges. To begin, Colectiv is a new platform established in 2021 with advanced data collection and potential for bidirectional communication functionalities that has required extra time to ensure accuracy and rigor. These delays introduced the need for additional support and communication with community partner organizations during intervention rollout to hold testing events and enroll participants at the events. The project also encountered turnover in anchor partner leadership and community partner staff in one of the project counties, resulting in challenges onboarding community partners and enrolling participants in those communities. In addition, the project is faced with overall “COVID-19 fatigue,” namely that participants are less motivated to attend events and enroll in a study that offers as its main incentive free COVID-19 testing and facilitated access to treatment. In addition, working remotely to lead a project in two communities presents challenges related to differences in time zones (to arrange team meetings), weather (such as major flooding in Merced County during partner onboarding), and communication (e.g., some partners preferred materials translated in languages not anticipated, such as Hmong, resulting in delays due to translation and institutional review board approval). These challenges are not atypical for community-engaged research [20], although the toolkit was a critical resource in addressing many of them.

Next steps for YMTT include continuing to offer enrollment and test kits at community partner–led events in both Merced and Pitt counties, distributing community partner email newsletters (see Fig. 4 for an excerpt from the first YMTT newsletter for sample topics and featured quotes from SYCT and YMCF studies), and improved bidirectional communication with community partners and participants. Specifically, the, Colectiv app will be used to administer surveys to both community partners and participants in order to determine health topics of interest, testing and treatment needs, and other community member issues that can be addressed in part with resource linkages, newsletter information, and more tailored communication and dissemination materials.

**Fig. 4 Fig4:**
[figure not shown]
Excerpt from sample You & Me: Test and Treat (YMTT) newsletter for community partners

## Conclusion

The YMTT study aims to reduce COVID-19 related health disparities through a community-engaged approach to test and treatment access. To achieve this goal, YMTT uses a tiered model of community-engaged research by leveraging large local organizations that are trusted by community partners and populations where timely health interventions are needed. Through this model, academic and other research organizations can effectively partner with community organizations to address health inequities. YMTT will provide evidence, using this tiered approach, to address COVID-19 testing and treatment disparities in two US counties. Future dissemination of YMTT findings, and the toolkit employed in this approach, will support effective and efficient community-engaged health interventions to close disparity gaps.

## Data Availability

The datasets used and/or analyzed during the current study are available from the corresponding author on reasonable request.
